### Intervention Group

The RA will meet each participant and conduct the pretest survey in the participant’s private hospital room. The computerized adaptive education intervention group will receive an advanced CKD education module with information about CKD risk factors, stages, treatment options, and lifestyle modifications. The RA will assist in advancing program modules but not offer any information or knowledge about CKD. The avatar will be an African American woman who will present statistics about African American individuals and CKD. The interactive component will allow participants to personalize the information received based on prior CKD knowledge, diabetes status, and the level of motivation. The interactive CKD video can be completed in 30-45 minutes. Following the patient’s completion of the advanced CKD education module, the RA will then readminister the General Health Knowledge and Intent survey.

The computerized adaptive education intervention group (and the usual health care control group) will complete the “What’s Next” form, to assess the patient’s commitment to specific self-care activities. Patients will select 3 health goals from a list of 10 options, rate their level of confidence in the ability to make change, and identify an action plan to accomplish each goal. Moreover, patients will be asked to report their needs from the medical care team and for community assistance, and they will be provided a resource list. The study will also ask if patients would like a primary care doctor and/or a nephrologist. This information will be relayed to the primary inpatient team. All the forms will be sent to the patient educator, a trained nephrology social worker.

We will encourage participants to complete the voluntary study in one visit. At 30 days after discharge, both groups will complete a follow-up call with the project RA. Participants will be queried about progress on goals set on the health commitment form, knowledge, and health intent.

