## Methods

### Trial Design

The I-C-CKD study is a hospital-based, randomized controlled trial of a computerized patient education intervention compared to usual hospital care. After obtaining verbal consent (Multimedia Appendix 1), each patient will be randomly assigned into two groups: usual hospital care (control group) and the computerized adaptive education (intervention group), which is assisted by a research assistant (RA).

The usual hospital care control group will feature a baseline General Health Knowledge and Intent survey. Participants in the usual hospital care control group will receive the pretest survey and education materials but will not receive specific knowledge about CKD or their CKD condition. Participants in the control group will receive printed patient education materials informing them of the importance of a general healthy lifestyle, including diet, physical activity, and medication adherence. The printed materials for the usual hospital care control group are meant for patients with cardiovascular conditions and do not have any information about CKD. Participants who receive the control condition will also be able to speak with the patient educator if they want to.

The computerized adaptive education intervention group will receive the advanced CKD education module with information on the risk factors, stages, treatment options, and lifestyle of patients with CKD (see Figures 1 and 2). The RAs will assist with the program but not offer any information or knowledge about CKD. Following the patient’s review of the advanced CKD education module, the RAs will administer the posttest General Health Knowledge and Intent survey.

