### Control Group

The RA will meet each patient and conduct the pretest survey in the participant’s private hospital room. The usual hospital care control group will receive the General Health Knowledge and Intent pretest survey and printed education materials without explicit CKD information or knowledge about their CKD condition. The distributed education materials were intended for patients with cardiovascular conditions and focus on the importance of a general healthy lifestyle, including diet, physical activity, and medication adherence, and does not include CKD specific information. Following the patient’s completion of the general health education video module, the RA will then readminister the General Health Knowledge and Intent survey.

The usual hospital care control group (and the computerized adaptive education intervention group) will complete the “What’s Next” form, to assess the patient’s commitment to 3 participant-selected self-care activities. Participants also will be contacted 30 days after discharge to complete the follow-up survey.

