### Statistical Methods

The planned total sample size is 170 (85 per group), which accounts for participant dropout due to unexpected discharges, changes in clinical status, or study disenrollment. The primary outcome will be measured by the change in baseline observed via the pretest, posttest, and follow-up surveys. Using a 2-sample, 2-tailed *t* test, a total of 154 (77 per group) participants is required to obtain >90% power to detect at least a 10% difference with the most conservative SD of 21% with a 1-sided type-1 error of 5%.

Our team will use the paired, 2-tailed *t* test with a Bonferroni adjustment for multiple comparisons with the usual hospital care and computerized adaptive education groups. We will use one-way ANOVA and chi-square tests to examine the significance between the usual hospital care and computerized adaptive education groups. This will determine whether there is a statistically significant difference between the two groups. We will also determine if the difference between observed and expected data is because of chance or a relationship between the usual health care and computerized adaptive education groups.

Data analysis will take place in an UCMC office. We will continue to monitor patient medical records after the study to determine whether they may be later included or excluded from the study.

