## Results

Recruitment for the I-C-CKD study began May 2, 2023. We are currently recruiting and have enrolled 96 patients who completed both pretest and posttest surveys as of December 2024. This includes 50 patients in the control group and 46 patients in the intervention group. Data analysis has not occurred. We will communicate trial results to trial participants, health care professionals, and the public via a journal publication.

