Limitations of this study include the single-hospital study design, which reduces the generalizability of the results. In addition, we are testing the intervention only among hospitalized African American patients who are generally admitted with urgent or acute health concerns, which may reduce their ability to fully participate or complete this study. An additional barrier for inpatient kidney education to be disseminated on a large scale is that the results may differ among a different group or in a different health care setting.

In conclusion, African American individuals often receive less patient education about self-care and medical treatments for CKD. We hope our study provides one way to reduce this disparity. However, to improve CKD outcomes, African American patients—and all patients with CKD—require frequent, understandable education about CKD across all sites of care.

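### Both arms' immediate posttest is worded as following completion of the education, so a patient who stops part-way but can still answer may go untested, possibly at different rates by arm

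*Protocol article*

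**What the plan says.** The immediate posttest appears in three places in the protocol article.

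- **Intervention Group:** the step follows the patient's "completion of the advanced CKD education module, the RA will then readminister the General Health Knowledge and Intent survey". The same section gives the length: "The interactive CKD video can be completed in 30-45 minutes".
- **Control Group:** the step follows the patient's "completion of the general health education video module, the RA will then readminister the General Health Knowledge and Intent survey".
- **Trial Design:** for the intervention arm the wording is looser: "review of the advanced CKD education module, the RAs will administer the posttest General Health Knowledge and Intent survey".

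The control exposure is described in two ways. Trial Design says "Participants in the control group will receive printed patient education materials informing them of the importance of a general healthy lifestyle", and the rest of Control Group also describes printed material. The video module appears only in the Control Group sentence on the posttest. No length is given for either form.

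The article expects some patients not to finish. Statistical Methods says that the sample size "accounts for participant dropout due to unexpected discharges, changes in clinical status, or study disenrollment". The Discussion says that patients are admitted with acute problems, "which may reduce their ability to fully participate or complete this study". Ethical Considerations provides a smaller payment for partly completed surveys. Results reports progress as follows: the investigators "have enrolled 96 patients who completed both pretest and posttest surveys as of December 2024", split as 50 control and 46 intervention.

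Primary Outcome takes change from baseline over the pretest, the posttest and the follow-up survey. The 30-day contact covers both groups and is not made conditional on finishing the material.

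**The concern.** A posttest that waits for completion makes receipt of the outcome depend on something that happens after randomisation: whether the patient gets through the assigned material. Some inpatients who tire, are called to a procedure or lose interest could still answer a questionnaire. The text makes no provision for testing them at that point.

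This matters for a comparison of arms if the hurdle differs between them. A 30-45 minute interactive video and a set of leaflets are not equally easy to finish. If the control exposure is the leaflets, the same wording sets a lower bar for controls. Patients with a posttest would then be selected more strongly in the intervention arm, and the randomised comparison of knowledge gain would no longer be protected.

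This is a rule about data collection. An analysis plan can define analysis sets and handle missing data, but it cannot recover a survey that was never given. The issue concerns patients who could still answer. It does not concern those withdrawn because they became too ill to take part.

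**Working it through.** **1. The plan's own figures.** Inputs from Statistical Methods: difference 10 points, SD 21 points, one-sided 5% error, power above 90%, 77 per group (154), enrolled 170 (85 per group).

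- Normal approximation: n per group = 2 × (1.645 + 1.282)² × 21² / 10² = 75.5, so 76.
- Exact t calculation: 77 per group, power 0.903. The stated 154 is reproduced.
- Dropout allowance: 170 − 154 = 16, and 16/170 = 9.4%. The article does not split this by arm.

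**2. Bias from testing finishers only.** Let a share m of the intervention arm have no posttest, and let those patients' gain be d points below the finishers' mean gain G.

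- Mean gain of the whole arm: (1 − m)G + m(G − d) = G − m·d.
- Mean gain of finishers: G.
- Overstatement in that arm: m·d.

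With loss in both arms, the bias in the difference is m_I·d_I − m_C·d_C. It is zero if loss and selection are equal, and it changes sign if the control term is larger or if d_I is negative.

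**3. Illustration.** The article gives neither m nor d. As yardsticks for m, take half the allowance falling in the intervention arm (8/85 = 9.4%) and all of it (16/85 = 18.8%), with no selection among controls. For d, take 5, 10 (the whole target difference) and 21 (one SD). All of these are assumptions.

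| m | d = 5 | d = 10 | d = 21 |
|---|---|---|---|
| 9.4% | 0.5 | 0.9 | 2.0 |
| 18.8% | 0.9 | 1.9 | 4.0 |

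Entries are bias in points. At d = 10 the range is about 9% to 19% of the 10-point target.

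**4. Effect on error and power.** With no true effect, 85 controls all tested and d = 10, the standard error is 21 × √(1/n₁ + 1/85), where n₁ is the number tested in the intervention arm.

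- m = 10% (n₁ = 76): SE 3.31, bias 1.0, one-sided type I error 9.0% instead of 5%.
- m = 20% (n₁ = 68): SE 3.42, bias 2.0, type I error 14.5%.
- One-sided power for a true 10-point difference, from the smaller n alone: 0.913 and 0.898.

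The risk is bias rather than lost power.

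**5. What the progress count can show.** Under 1:1 allocation, 46 of 96 completers in the intervention arm gives an exact binomial p of 0.76. There is no sign of a large imbalance. Because the numbers randomised per arm are not given, differential loss cannot be excluded either.

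**The case against.** The strongest reply is that these sentences give the order of procedures and do not exclude anyone. A posttest naturally follows the material it tests. Nothing says that a patient who stops early is refused one. Trial Design speaks only of review, and completing the study in one visit is encouraged, not required, so an interrupted patient might resume. Analysis sets and the handling of interrupted sessions may sit in a full protocol or analysis plan that is not shown. This reply largely stands, and it is why the point says that such a patient *may* go untested. It does not remove the point: the only trigger written for the RA under both group headings is completion, and a missed posttest cannot be restored at analysis.

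A reader might infer something stronger: that patients who stop have no primary outcome at all, so that intervention finishers are compared with nearly all controls. The documents do not support this.

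- The primary outcome also uses the follow-up survey, and the 30-day call asks both groups about knowledge without regard to completion. That measure does not replace the immediate posttest, but it is not nothing.
- Control Group carries the same completion wording, so no source shows that nearly all controls are tested.
- With no control duration stated, a longer intervention exposure is itself an inference.

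The direction of bias is also open. Finishers may be less ill and more motivated. But the outcome is a change score, and better-informed finishers may have less room to gain. The dropout allowance used for m covers other causes, including clinical decline. Comparable selection among controls would offset part of the bias.

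**Conclusion.** The point holds as a weakness in how the posttest is fixed, not as a demonstrated bias. Both arms' wording can leave a randomised, pretested patient who is still able to answer without an immediate posttest. The control exposure is described inconsistently and has no stated length, so the arms may not lose patients equally. Counting progress as completers of both surveys hides any such loss.

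Size and direction cannot be established from the article. The range of 0.9 to 1.9 points rests on two assumptions: that 9.4% to 18.8% of the intervention arm alone is lost, and that those patients would have gained 10 points less. The 50 v 46 split gives no sign of large differential loss. The change is worth making because it removes a selection step after randomisation at very little cost. With 96 of 170 enrolled at the time of writing, it could still apply to patients yet to be recruited.

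**What to change.** In Trial Design, Intervention Group and Control Group, replace the completion and review wording with one rule for both arms: *The posttest is offered to every randomised participant able to answer, at the end of the education session or before discharge, whether or not the material was completed.*

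In addition:

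- keep these patients in their randomised arm;
- report numbers randomised, pretested and posttested by arm, in place of a single count of completers;
- reconcile the printed and video descriptions of the control material.

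The cost is a wording change and a flow count by arm, with no extra staff or visits. Including partly exposed patients may make the observed difference slightly smaller. The rule will not reach everyone: a patient who is discharged unexpectedly before the RA can return will still be missed.

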### Control Group

The RA will meet each patient and conduct the pretest survey in the participant’s private hospital room. The usual hospital care control group will receive the General Health Knowledge and Intent pretest survey and printed education materials without explicit CKD information or knowledge about their CKD condition. The distributed education materials were intended for patients with cardiovascular conditions and focus on the importance of a general healthy lifestyle, including diet, physical activity, and medication adherence, and does not include CKD specific information. Following the patient’s completion of the general health education video module, the RA will then readminister the General Health Knowledge and Intent survey.

The usual hospital care control group (and the computerized adaptive education intervention group) will complete the “What’s Next” form, to assess the patient’s commitment to 3 participant-selected self-care activities. Participants also will be contacted 30 days after discharge to complete the follow-up survey.

### Outcomes

#### Primary Outcome

The primary outcome of this study is the changes in patient knowledge, attitudes, and behavior about CKD and RRT. To evaluate CKD and CKD self-care knowledge, we will use a modified Kidney Knowledge Survey; the CKD Self-Management Knowledge Toolkit, which is a validated instrument [8,9]; and an investigator-developed ESKD knowledge survey. We will measure the change from the baseline observed via the pretest, posttest, and follow-up surveys. The pretest and posttest surveys comprise 20 mixed format multiple-choice and Likert-scale questions (ranging from strongly agree to strongly disagree; from no knowledge to a great deal of knowledge; and from extremely unlikely to extremely likely) to examine the patient’s basic understanding of their health, general CKD knowledge, and health management.

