### Primary Hypothesis

Our primary hypothesis is that the computerized adaptive education will be more effective than usual hospital care in improving knowledge about CKD, CKD self-care, and RRT options (primary outcome).

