**Figure 2 figure2:**
[figure not shown]
Screenshot of the computerized adaptive education intervention regarding treatment options. CKD: chronic kidney disease.

Both the usual hospital care control group and the computerized adaptive education intervention group will complete the “What’s Next” form, to assess the patient’s commitment to specific self-care activities. Patients will select their top-3 health goals, rate how confident they are about each goal, and identify how important each goal is to them. Patients will also report on their health resources. All the forms will be sent to the patient educator, a trained nephrology social worker.

Each patient will be contacted 30 days after discharge to ask about their commitment to health goals, barriers to self-care, and treatment plans.

The SPIRIT (Standard Protocol Items: Recommendations for Interventional Trials) checklist is provided in Multimedia Appendix 2.

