#### Secondary Outcomes

The secondary outcomes are patient motivation and intent. We will administer the CKD Self-Efficacy Scale [10], the Patient Activation Measure [11], and the Kidney Failure Treatment Preferences [12] before the intervention, immediately after the intervention, and at 30 days after discharge. We will administer the General Health Knowledge and Intent survey, an investigator-developed instrument, to assess RRT preferences and commitment to CKD self-care activities, including intent to seek a nephrologist, noncatheter dialysis access initiation, and completion of a transplant evaluation. Each patient will be contacted 30 days after discharge to discuss their commitment to each selected health goals, barriers, and treatment plan.

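### The primary outcome is knowledge alone in the hypothesis but knowledge, attitudes and behavior in the outcomes section, with no single score or time point named, while the sample size covers one comparison only

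*Protocol article*

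**What the plan says.** **Domain.** In the Protocol article, Primary Hypothesis concerns "improving knowledge about CKD, CKD self-care, and RRT options (primary outcome". Secondary Hypothesis then covers intent, and action and commitment to health-seeking behavior. The Primary Outcome section has a wider definition: "The primary outcome of this study is the changes in patient knowledge, attitudes, and behavior about CKD and RRT".

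**Instrument.** For knowledge, Primary Outcome says "we will use a modified Kidney Knowledge Survey; the CKD Self-Management Knowledge Toolkit, which is a validated instrument", and adds "an investigator-developed ESKD knowledge survey". It ties no instrument to attitudes or behavior. It describes the pretest and posttest as "20 mixed format multiple-choice and Likert-scale questions". Trial Design, Intervention Group and Control Group call the survey given before and after the education the General Health Knowledge and Intent survey. That survey appears under Secondary Outcomes: "We will administer the General Health Knowledge and Intent survey, an investigator-developed instrument, to assess RRT preferences and commitment" to self-care activities.

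**Time.** Primary Outcome says "We will measure the change from the baseline observed via the pretest, posttest, and follow-up surveys", and Statistical Methods repeats this. Follow-up is the call 30 days after discharge.

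**Sample size and multiplicity.** Statistical Methods gives one calculation: 154 participants (77 per group) for more than 90% power, a 10% difference, SD 21% and a one-sided 5% error, with 170 enrolled. It names no instrument, domain or time point for that difference. A Bonferroni adjustment is attached to paired t tests, without a number of comparisons.

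**The concern.** Two current definitions of the primary outcome cannot both hold. Behavior is primary in one section and, as action and health-seeking behavior, secondary in another. An unseen analysis plan could add detail, but it would not remove a conflict between two statements in the protocol itself.

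The instrument and the time point are open as well. A reader cannot tell whether the 10% difference refers to one of the three knowledge instruments, to the 20-item survey, or to the General Health Knowledge and Intent survey, nor whether the last two are the same thing. As the text stands, more than one combination of domain, instrument and time could be called primary once results are known. The power statement, meanwhile, supports one comparison.

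**Working it through.** **Inputs** (Statistical Methods): difference δ = 10, SD σ = 21, n = 77 per group, one-sided α = 0.05, two-sample t test, equal allocation.

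**1. Reproduce the stated figure.**
- Noncentrality = δ / (σ√(2/n)) = 10 / (21 × √(2/77)) = 10 / 3.384 = 2.955, with 2 × 77 − 2 = 152 degrees of freedom.
- Normal approximation: power = Φ(2.955 − 1.645) = Φ(1.310) = 0.905.
- Noncentral t: power = 0.903, and 77 is the smallest n per group that reaches 0.90.

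So 77 per group is right on its own inputs. It uses the whole 5% for one comparison.

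**2. Allow for more than one primary comparison.** Suppose that success on any one of k comparisons would count, that Bonferroni is applied (one-sided α = 0.05/k), and that each score has the same 10% difference and SD 21%. The normal approximation is Φ(2.955 − z), where z is the upper 0.05/k point. The article does not give k; these values are assumptions.

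| k | Example | z | Power at 77, normal | Power at 77, noncentral t | n per group for 90%, noncentral t |
|---|---|---|---|---|---|
| 1 | one score, one time | 1.645 | 0.905 | 0.903 | 77 |
| 2 | one score, two times | 1.960 | 0.840 | 0.835 | 94 |
| 3 | three instruments or three domains, one time | 2.128 | 0.796 | 0.790 | 104 |
| 6 | three by two times | 2.394 | 0.713 | 0.703 | 121 |

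Power here is for a given comparison.

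**3. If all comparisons had to succeed instead.** No split of α is needed, but joint power falls. For k = 2 it lies between 2 × 0.903 − 1 = 0.806 and 0.903, depending on correlation. The article does not say which success rule applies.

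**4. Does the planned Bonferroni adjustment already cover this?** No. It is tied to paired tests, its number of comparisons is not given, and step 1 shows that the sample size does not include it.

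**The case against.** The strongest reply is that the intention can be guessed. The hypothesis says knowledge. The listed dropout reasons begin with in-hospital events, and Results counts patients who completed pretest and posttest. All of this points to knowledge at the in-hospital posttest, for which 77 per group is adequate. Item-level scoring is also commonly left to the full protocol or analysis plan, which are not shown. Both points are fair. The second means that a missing list of scored items is no finding. The first is an inference that the outcomes section contradicts, so the conflict stands.

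Several stronger readings are tempting but not supported:

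- **Six primary tests with about a 26% chance of a false positive.** This is 1 − 0.95⁶ = 0.265, which takes six independent, unadjusted tests at 5%. The article does plan a Bonferroni adjustment, scores from the same patients are correlated (which lowers the figure), and six is a constructed count.
- **A larger loss of power from a two-sided α.** That brings in a separate matter, the one-sided error stated alongside a 2-tailed test. The fair comparison stays one-sided.
- **Poor power at 30 days because of dropout.** The article gives no 30-day retention figure. It gives only the overall allowance, 1 − 154/170 = 9.4%.
- **Knowledge is not collected at 30 days.** Trial Design does say "Each patient will be contacted 30 days after discharge to ask about their commitment to health goals, barriers to self-care, and treatment plans", without mentioning knowledge, but Intervention Group says that both groups have the call and includes knowledge in it.
- **Right-or-wrong and Likert items are summed into one score.** The article says only that both kinds are present.
- **The trial is unblinded.** Blinding says that participants are not told their group; only the research team is unblinded.

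**Conclusion.** The concern holds as an internal contradiction. The domain of the primary outcome differs between sections, the survey actually repeated at posttest is classed as secondary, and no primary time point is named. The stated power of more than 90% is correct for one comparison (90.3% at 77 per group). It becomes about 84%, 79% or 70% per comparison if two, three or six are carried under Bonferroni.

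Those lower figures rest on assumed counts, on any single success being enough, and on the same difference and SD for every score. They show what is at stake in leaving the endpoint open; they are not an error in the 154. Recruitment is under way (96 patients had completed both surveys by December 2024), but the article states that no analysis has been done, so the choice can still be made before results are seen.

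**What to change.** Before any analysis, reconcile Primary Hypothesis, Primary Outcome, Secondary Outcomes and Statistical Methods as follows:

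- Name one primary endpoint: a score for knowledge of CKD, self-care and RRT, from a named instrument, at one time point (for example the in-hospital posttest), compared between groups with the pretest score as covariate.
- Say how the three knowledge instruments, the 20-item pretest and posttest, and the General Health Knowledge and Intent survey relate, so that the primary score is not drawn from a survey listed only as secondary.
- Make 30-day knowledge, which is already planned, and the attitude, self-rated, intent and behavior measures secondary.
- State that the 10% difference and SD 21% refer to the primary score. If more than one primary comparison is kept, state the number and the success rule, and redo the sample size.

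With one endpoint, the 77 per group stands on the article's own one-sided basis. The change is to wording only, with no new patients or data. The cost is less breadth in what can be called primary.

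### No primary time point or score is named for a primary outcome measured at two time points on several instruments; the sample size covers one comparison and ignores the stated Bonferroni adjustment

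*Protocol article*

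**What the plan says.** **Time points.** The Primary Outcome section states: "We will measure the change from the baseline observed via the pretest, posttest, and follow-up surveys". Statistical Methods repeats it almost word for word: "The primary outcome will be measured by the change in baseline observed via the pretest, posttest, and follow-up surveys". The 30-day call does return to knowledge (Intervention Group): "Participants will be queried about progress on goals set on the health commitment form, knowledge, and health intent". Neither post-baseline time point is called primary.

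**Instruments.** To evaluate knowledge, "we will use a modified Kidney Knowledge Survey; the CKD Self-Management Knowledge Toolkit, which is a validated instrument", "and an investigator-developed ESKD knowledge survey". The same section adds: "The pretest and posttest surveys comprise 20 mixed format multiple-choice and Likert-scale questions". It does not say whether these items form one total.

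**Scope.** The Primary Outcome section opens: "The primary outcome of this study is the changes in patient knowledge, attitudes, and behavior about CKD and RRT". The Primary Hypothesis is narrower: the intervention is expected to be "more effective than usual hospital care in improving knowledge about CKD, CKD self-care, and RRT options (primary outcome").

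**Sample size and tests.** Statistical Methods requires 77 per group for more than 90% power at a 10% difference, with an SD of 21% and a one-sided 5% error; 85 per group allows for dropout. The analysis sentence names a paired t test with a Bonferroni adjustment, and the Abstract (Methods) links that test to the pretest, posttest and follow-up results. The between-group tests, one-way ANOVA and chi-square, come in a separate sentence that mentions no adjustment.

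**The concern.** A gain measured just after a 30-45 minute module and a gain still present 30 days after discharge support different conclusions. As worded, either could be presented as the primary result, on any of the listed instruments or on a total.

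The Blinding section says that the research team is not blinded, and under Randomization and the two group sections the research assistant both allocates participants and administers the surveys. In that setting the choice of primary comparison should not remain open once data are seen.

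Two things are at stake. If several comparisons each count at 5%, the error rate of the primary claim rises. If they are adjusted, the planned size no longer gives the stated power.

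**Working it through.** **Inputs from Statistical Methods:** difference 10 and SD 21 (read as percentage points on one scale), 77 per group, one-sided alpha 0.05, target power 90%.

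**1. Reproducing the plan's figure.**
- n per group = 2 × (SD/difference)² × (z₁₋α + z₀.₉₀)² = 2 × 4.41 × (1.645 + 1.282)² ≈ 75.5, so 76. The exact t calculation gives 76.2, so 77.
- Power at 77 per group = Φ(10 / (21 × √(2/77)) − 1.645) = Φ(2.955 − 1.645) = 90.5% (t: 90.3%).

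The stated 77 is therefore one comparison at an undivided one-sided 5%. Nothing is held back for a second test.

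**2. Counting the comparisons.** The article gives no count.
- Lower reading: one total score at two time points, 2 tests.
- Upper reading for knowledge: three instruments at two time points, 3 × 2 = 6 tests.
- If attitudes and behavior count as separate primary outcomes, there are more.

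**3. If Bonferroni covers the primary comparisons.** Power per test = Φ(2.955 − z₁₋α/m), assuming the same difference and SD for every test.

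| Tests (m) | One-sided alpha per test | Power at 77 per group | Per group for 90% |
|---|---|---|---|
| 1 | 0.05 | 90.5% (t: 90.3%) | 76 (t: 77) |
| 2 | 0.025 | 84.0% (t: 83.5%) | 93 (t: 94) |
| 6 | 0.00833 | 71.3% (t: 70.3%) | 120 (t: 121) |

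With two-sided tests, the power at 77 per group is 76.2% (t: 75.5%) for two tests and 62.4% (t: 61.1%) for six. The sizes exclude dropout. These are powers per test; the chance of succeeding on at least one test is higher.

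**4. If Bonferroni does not cover them.** For independent tests, the chance of at least one false positive is 1 − 0.95² = 9.8% for two and 1 − 0.95⁶ = 26.5% for six. Measures on the same patients will be correlated, but the article gives no correlations, so a range is assumed. Simulation with equally correlated normal test statistics (1,000,000 draws) gives:

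| Tests | Assumed correlation | One-sided 5% | Two-sided 5% |
|---|---|---|---|
| 2 | 0.3 | 9.3% | 9.5% |
| 2 | 0.5 | 8.8% | 9.0% |
| 2 | 0.7 | 8.1% | 8.3% |
| 2 | 0.9 | 6.8% | 7.0% |
| 6 | 0.3 | 22.0% | 24.2% |
| 6 | 0.5 | 18.5% | 20.7% |
| 6 | 0.7 | 14.8% | 16.4% |
| 6 | 0.9 | 10.0% | 10.8% |

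**The case against.** The strongest reply is that the plan is not silent on multiplicity. Bonferroni is stated in both the Abstract and Statistical Methods, and the Abstract ties it to the three surveys over time. If it is applied to the primary comparisons, the error rate is held. This stands, and it rules out a flat statement that the type I error exceeds 5%. It does not settle the matter: the adjustment is attached to a paired test, the number of comparisons is not given, the between-group tests that address the hypothesis carry none, and the sample size ignores it.

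Second, six tests is a reading and not a stated count. A 20-question survey and a single percentage scale in the power statement are compatible with one total score, which leaves two tests. The group sections name only the General Health Knowledge and Intent survey as the one repeated at posttest. This also stands, so six is shown only as an upper reading.

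Third, the immediate posttest is arguably implied. Results counts participants who completed pretest and posttest, and the listed dropout reasons are largely in-hospital events. That is a good reason to choose the posttest, but the outcome definition still includes follow-up in both places where it appears.

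Finally, a split-result rule, a testing sequence and the Bonferroni family may sit in an analysis plan that is not shown, so their absence is not held against the article. The point rests on what it does state: an open definition given twice, a primary outcome wider than its hypothesis, and a size for one test.

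**Conclusion.** The point holds in a conditional form. The article defines its primary outcome over two time points and several instruments, names no primary comparison, and sets its primary outcome wider than its primary hypothesis. Followed as written, the plan pays in one of two ways:

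- **Adjusted:** the stated power of more than 90% becomes about 84% with two tests and about 70% per test with six (one-sided, 77 per group).
- **Unadjusted:** the chance of at least one false positive is about 7% to 9.5% with two tests and about 10% to 24% with six.

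These figures assume a 10-point difference and SD of 21 for every comparison, and correlations of 0.3 to 0.9 that are not in the document.

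A reader might infer that success may be claimed on any one of six tests with error certainly above 5%. The document does not support that. It states no any-one-wins rule and no count of six, and it does promise an adjustment.

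**What to change.** Amend the Primary Outcome and Statistical Methods sections before any analysis:

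- **Primary comparison:** the between-arm difference in change from pretest to immediate posttest in one knowledge score.
- **Score:** list the items that make it up. Use those with a correct answer that cover CKD, CKD self-care and RRT options. Leave out the Likert items on agreement, self-rated knowledge and likelihood, which cannot be marked correct.
- **Scope:** move attitudes and behavior to secondary outcomes so that the primary outcome matches the primary hypothesis, and state this narrowing openly.
- **First secondary outcome:** the 30-day change in the same score, tested at full alpha only if the primary is significant. Claim retention of knowledge only from this test. The 30-day call must carry the same items; the article says only that knowledge is asked.
- **Separate instruments:** report them as supportive.

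No alpha is then split, and the one-comparison sample size applies. Statistical Methods also calls the test 2-tailed while using a one-sided error; that is a separate issue to resolve.

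The cost is wording in the protocol and registry. Results states that no analysis has occurred, so the change can still be made credibly. The downside is that a positive result on one instrument alone, or only at 30 days, no longer counts as primary success.
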